### Data Collection and Missing Data

Clinical data including patient demographics, diagnosis, medical histories, clinical and laboratory characteristics, medication treatment, procedural details and main outcomes were obtained through review of electronic medical records. The principal data, such as clinical outcomes, were collected by two investigators independently, and inconsistent data were verified by a third investigator.

Variables were included as candidates for this risk score after removing variables with ≥ 10% missing values (Table 1), and for those with incomplete data, we assumed that patients with the missing data ≤ 5% occurred at random depending on the clinical variables and used multiple imputations. This risk score model was developed based on imputed complete cases.

**Table 1 T1:** Observations and endpoints.

**Category**	**Method and materials**	**Observation and examination items**
Demographic characteristics	Interview	Age, sex and smoking status.
STEMI	Medical examination and interview	Onset of STEMI, date of hospitalization, description of treatment.
History of present illness/previous history/therapies	Interview	Previous history of cardiovascular and cardiovascular risk-related diseases and history of treatment (Hypertension, MI, CABG, COPD, AF, stroke, PCI, sudden cardiac arrest, thrombolysis, pericardial effusion, PCI lesion).
Physical findings	Medical examination	SBP, DBP, heart rate and Killip class.
Family history	Interview	Coronary artery diseases, hypercholesterolaemia and ischaemic cerebral infarction in relatives to the second degree of kinship.
Hematological and biochemical examinations	Serum and urine	The following parameters will be measured from blood acquired within 24 h after admission: WBC, eGFR, creatinine, albumin, hemoglobin, TG, TC, total bilirubin, direct bilirubin, LDL, HDL, ALT, CO_2_ combining power, Urine PH.
Heart function	Echocardiography	LVEF, LVDd, LVDs.
Medication during hospital stay	Electronic medical record	Statins, Warfarin, Tirofiban, ARB, CCB, ACEI, β-blockers, insulin, metformin, PPI, diuretics and nitrates.
Procedural characteristics	Electronic medical record	PCI approach, multi-lesion, contrast volume, number of stents and total length of stents.

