#### Data Analysis

The student's *t*-test or Wilcoxon rank-sum test was used to compare the continuous variables and the chi-square test or Fisher exact test was used as appropriate for categorical variables for the comparison of patients with or without infections in both datasets.

The risk score was developed using a backward stepwise logistic regression model. All candidate predictors were included in the development of the risk score, and to avoid overfitting data and select the best subset of risk factors, a bootstrap method was used. For missing data, 10 multiple imputations were performed using the SAS MI procedure, and 100 bootstrap repeats were conducted for each imputation. Variables selected in at least 90% of 1,000 bootstrap repeats were included in the final model. The risk score was developed for each imputed data via using the selected variables and the SAS MIANALYZE procedure was used to combine the results of the analyses. For this risk score, the scoring method was analogous to that of Sullivan et al. (21) and was used based on the developed risk score. For the scoring purpose, continuous variables were categorized into groups regarding the clinical significance. The risk score of post-AMI consisted of four levels (low-risk, moderate-risk, high-risk, and very high-risk) in order to enhance the clinical utility.

Both discriminatory accuracies assessed by the C-statistic and calibration measured by the Hosmer-Lemeshow χ^2^ statistic and calibration plot were used to evaluate the predictive accuracy of the risk score. The bootstrap method with 1,000 bootstrapped replications was used to perform an internal cross-validation of the risk score. The average of the C-statistic was reported. In addition, external validation and subgroup validation (older, gender, diabetes, anemia, and chronic kidney disease) of the risk score model was conducted to assess the stability of the model. The risk score was also validated in patients with NSTE-ACS undergoing PCI, and the area under curve (AUC) of this risk score was compared to the previous scoring systems (6, 7). Furthermore, comparison of the area under the receiver operating characteristic (ROC) curve was according to the nonparametric approach of DeLong et al. (22). To evaluate the clinical utility of this risk score, decision curve analysis was introduced and the risk score with a higher net benefit indicated a better clinical effect (23).

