Infection is known to have unacceptably high and alterable mortality. Thus, early risk stratification of patients is a crucial clinical task. Some studies have reported the risk scores or markers to assess the probability of infection in patients with cardiovascular diseases or in critically ill patients. Fowler et al. developed a simplified risk score with twelve variables to identify high-risk for major infection in patients undergoing cardiac surgery (9). The variables included in this risk score were age, body mass index (BMI), diabetes, renal failure, congestive heart failure, peripheral vascular disease, female gender, chronic lung disease, cardiogenic shock, myocardial infarction, concomitant surgery and intraoperative variables including perfusion time and intra-aortic balloon pump. The model that limited to preoperative characteristics and combined model including both preoperative and intraoperative characteristics achieved a *C*-index of 0.697 and 0.708, respectively. Therefore, the discriminatory accuracies of these prediction models were relatively low, and the model only reflected the overall clinical objective due to broader definitions (9). Raja SG et al. reported that the Brompton Harefield Infection Score (BHIS) could effectively predict surgical site infection (SSI) risks and contribute to risk stratification in patients following coronary artery bypass graft (CABG) (24). The baseline risk score consisting of female, diabetes or HbA1c >7.5%, BMI ≥ 35, LVEF <45% and emergency surgery offered an effective predictive ability (ROC curve was 0.727). However, this model had several limitations, the relatively small number of SSI events (n=96) limited the ability to identify associations with a large number of variables. Additionally, the accuracy and utility of the BHIS score tool were only validated internally but not in an external dataset (24). Furthermore, several other risk score models, such as the intensive care infection score and the clinical pulmonary infection score were established to assess the infection risks in critically ill patients (25, 26). However, their practical utility was limited because of the lower predictive value (25) and the circumscribed application to pulmonary infection (26). Up to now, few studies have proposed an infection prediction model for patients with STEMI before our recent researches, and there is no scoring system established specifically to assess patients' individual risk of infection among STEMI following PCI. Therefore, this study aimed to develop and validate a novel risk score based on risk factors for early prediction of infection in these patients.

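### Diabetes is a planned validation subgroup but has no item in Table 1, where in-hospital insulin and metformin stand as candidate predictors instead

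*Protocol article*

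**What the plan says.** Under Data Analysis, the protocol article commits to external validation and "subgroup validation (older, gender, diabetes, anemia, and chronic kidney disease" to judge the stability of the model. The same section enters every candidate predictor into backward stepwise logistic regression with bootstrap selection.

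Under Data Collection and Missing Data, the candidates are described with a reference to the table: "Variables were included as candidates for this risk score after removing variables with ≥ 10% missing values (Table 1". The relevant rows of Table 1 are:

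- **History.** The heading is "Previous history of cardiovascular and cardiovascular risk-related diseases and history of treatment", and the items in brackets are "Hypertension, MI, CABG, COPD, AF, stroke, PCI, sudden cardiac arrest, thrombolysis, pericardial effusion, PCI lesion".
- **Laboratory, within 24 h of admission.** "WBC, eGFR, creatinine, albumin, hemoglobin, TG, TC, total bilirubin, direct bilirubin, LDL, HDL, ALT, CO_2_ combining power, Urine PH".
- **Medication during hospital stay.** "Statins, Warfarin, Tirofiban, ARB, CCB, ACEI, β-blockers, insulin, metformin, PPI, diuretics and nitrates".

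The Discussion describes two earlier infection scores in enough detail to show their predictors, and diabetes is in each. For the surgical-site score it writes: "The baseline risk score consisting of female, diabetes or HbA1c >7.5%, BMI ≥ 35". The stated aim throughout, from the Abstract to the conclusion, is early prediction of infection.

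**The concern.** Two things follow if the data items are taken as printed.

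First, the diabetes subgroup has no named source or definition. It could be formed later from a recorded diagnosis, from drug use or from a laboratory value, and each route would select different patients.

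Second, and more important, the listed candidates contain two diabetes drugs and not the disease. Diabetes is a baseline fact that can be known at admission. Insulin or metformin given at some point in the stay is not. Nothing in Table 1 limits the medication row to the period before infection, so an entry there could reflect care given after the outcome had occurred. If such a variable entered the score, apparent discrimination could be inflated by information unavailable when the score is meant to be used.

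The gap could carry into validation. The Study Population section requires complete data in the validation cohort only for the risk factors identified in development. If diabetes is never a candidate, nothing stated secures its recording in that cohort, in the other centers or in the earlier NSTE-ACS cohort.

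**Working it through.** **1. Planned subgroups against Table 1**

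| Subgroup | Listed item that can define it |
|---|---|
| Older | Age |
| Gender | Sex |
| Anemia | Hemoglobin |
| Chronic kidney disease | eGFR, creatinine |
| Diabetes | None |

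Four of the five map to a listed item.

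**2. Item count**

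Items named in the history row: 11. Laboratory: 14. Medication: 12. Demographic, physical, echocardiographic and procedural rows together: 3 + 4 + 3 + 5 = 15. Total: 11 + 14 + 12 + 15 = 52. None of the 52 is diabetes, glucose or HbA1c. Two, insulin and metformin, are diabetes drugs. The count leaves out the STEMI, family-history and endpoint rows, which do not mention diabetes either. The Laboratory Testing section names neither glucose nor HbA1c.

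**3. How good the proxy is**

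Insulin or metformin during the stay misses patients whose diabetes is managed by diet or by other drugs. In-hospital insulin also does not prove a prior diagnosis. So the pair neither contains all patients with diabetes nor only those patients.

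**4. Timing**

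The laboratory row is fixed to the first 24 h after admission. The medication row covers the hospital stay, and so does the primary endpoint. Predictor and outcome therefore share one window, with no stated order between them. This holds for all 12 drugs in the row, not only for insulin and metformin.

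**5. Effect of the change on sample size**

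The protocol's own figure comes first: 8 factors × 10 events per variable = 80 infections, and 80 / 0.10 = 800 patients. This reproduces the stated minimum. Adding diabetes and removing insulin and metformin changes the listed items from 52 to 52 − 2 + 1 = 51. The cap of 8 factors is untouched, so the minimum stays at 800. Only if the sponsor raised the cap to 9 would the same rule give 9 × 10 = 90 infections and 90 / 0.10 = 900 patients.

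**The case against.** The strongest reply is that Table 1 is not a complete inventory. The Laboratory Testing section mentions electrolytes, cardiac enzymes, body temperature and respiration rate, none of which is in Table 1, and it leaves room for other routine tests. The history heading is wide enough to include diabetes, and the source is the electronic record with medical histories. All of this stands. A reader might infer that the subgroup cannot be formed, or that diabetes cannot be a candidate; the document does not support either inference.

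It can also be said that the table reference is loosely placed and that Table 1 mixes candidates with endpoints and dates. That is fair, but no other candidate list is given, so Table 1 is the only place where a reader can learn what was tested. A subgroup variable need not be a predictor, which is also true, and the subgroup gap alone would be close to omitted detail in a condensed article. The candidate question is different: the article prints specific items, and they include the treatments without the disease.

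A reader might take the Discussion to show that every infection score under review uses diabetes. It does not. Four infection scores are named there, and diabetes appears in the two whose predictors are listed, both from cardiac surgery. The Introduction also cites a score of age, creatinine and ejection fraction that was validated for post-AMI infection and does not contain diabetes. The earlier scores make diabetes a reasonable candidate; they do not make it a mandatory one.

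Finally, selection requires a variable to appear in at least 90% of 1,000 bootstrap repeats, so neither drug need enter the score. That is correct, but a stable association is no protection against a predictor recorded after the outcome.

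**Conclusion.** The point holds as a mismatch between the listed data items and the planned analysis. One of five subgroup validations has no listed source, and the printed items offer two whole-stay drugs as the only trace of a diagnosis that can be known at admission. The second part carries the weight, because it conflicts with the aim of early prediction.

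This rests on reading Table 1 as the candidate list, which is the natural reading of the reference to it. It does not rest on any claim that diabetes was not recorded; it probably was. Nor does the document show that insulin or metformin was selected: the Introduction mentions seven predictors without naming them.

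No numerical size can be put on the resulting bias. A reader might size the subgroup from an assumed prevalence of diabetes, but the article gives none, and the result would describe how large the subgroup is, not the error caused by the mismatch.

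**What to change.** - Add diabetes to the history row of Table 1, defined as a diagnosis known before or at admission and taken from the electronic record.
- Define the diabetes subgroup by that item in every cohort where the subgroup validation is run.
- Enter diabetes as a candidate predictor in place of in-hospital insulin and metformin.
- For the other ten drugs in the medication row, apply the same timing test: keep a drug as a candidate only if its use is recorded by the time the score is to be calculated.

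The cost is one extra field from records already being reviewed and one table edit. If variable selection has already been run, it would have to be repeated with the changed candidate list. The stated minimum of 800 patients is unchanged under the cap of 8 factors.

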## Discussion

The results of this study will develop and validate a relatively simple risk score based on easily acquired clinical variables to identify the patients with STEMI undergoing PCI at high-risk of post-AMI infection. In addition, the predictive accuracy of this risk score will be validated in several subgroups and an external validation cohort including patients with NSTE-ACS.

Infection is known to have unacceptably high and alterable mortality. Thus, early risk stratification of patients is a crucial clinical task. Some studies have reported the risk scores or markers to assess the probability of infection in patients with cardiovascular diseases or in critically ill patients. Fowler et al. developed a simplified risk score with twelve variables to identify high-risk for major infection in patients undergoing cardiac surgery (9). The variables included in this risk score were age, body mass index (BMI), diabetes, renal failure, congestive heart failure, peripheral vascular disease, female gender, chronic lung disease, cardiogenic shock, myocardial infarction, concomitant surgery and intraoperative variables including perfusion time and intra-aortic balloon pump. The model that limited to preoperative characteristics and combined model including both preoperative and intraoperative characteristics achieved a *C*-index of 0.697 and 0.708, respectively. Therefore, the discriminatory accuracies of these prediction models were relatively low, and the model only reflected the overall clinical objective due to broader definitions (9). Raja SG et al. reported that the Brompton Harefield Infection Score (BHIS) could effectively predict surgical site infection (SSI) risks and contribute to risk stratification in patients following coronary artery bypass graft (CABG) (24). The baseline risk score consisting of female, diabetes or HbA1c >7.5%, BMI ≥ 35, LVEF <45% and emergency surgery offered an effective predictive ability (ROC curve was 0.727). However, this model had several limitations, the relatively small number of SSI events (n=96) limited the ability to identify associations with a large number of variables. Additionally, the accuracy and utility of the BHIS score tool were only validated internally but not in an external dataset (24). Furthermore, several other risk score models, such as the intensive care infection score and the clinical pulmonary infection score were established to assess the infection risks in critically ill patients (25, 26). However, their practical utility was limited because of the lower predictive value (25) and the circumscribed application to pulmonary infection (26). Up to now, few studies have proposed an infection prediction model for patients with STEMI before our recent researches, and there is no scoring system established specifically to assess patients' individual risk of infection among STEMI following PCI. Therefore, this study aimed to develop and validate a novel risk score based on risk factors for early prediction of infection in these patients.

This observational study protocol has several limitations. First, this risk score was exclusive to STEMI patients and validated in patients with NSTE-ACS, clinicians should take special cautions when applying these results to other patients, such as stable coronary artery disease. Second, infection was difficult to diagnose to some extent and would be overestimated sometimes. However, the infection in this study was those treated with antibiotics which were strictly confirmed and approved by the hospital infection control committee. Third, the candidate risk variables are limited to those available in the patient cohort of this study. The more variables the scoring system contains, the higher the predictive accuracy of the risk score achieved. Finally, the current risk score did not include any new biomarkers. Incorporating new biomarkers may create a more robust model. However, this risk score was derived from clinical data routinely collected and would be more accessible in clinical practice.

In conclusion, to the extent of our knowledge, our risk score will be the first risk model for early prediction of infection in patients with STEMI undergoing PCI. This simple tool may therefore improve evaluation of post-AMI infection and enhance future researches into the best practices to prevent or reduce the infection in such patients.

## Ethics Statement

The studies involving human participants were reviewed and approved by Ethics Committee of Guangdong Provincial People's Hospital. The patients/participants provided their written informed consent to participate in this study.
